#### 2.2.2. Collecting Discarded Packs from Streets

In addition to collecting empty packs from the tobacco retailers, discarded packs from the streets where those retailers are established and also from some other locally important streets around public gathering places will be accumulated [3]. The distance that would be covered in each street would be one kilometer (half a kilometer in each direction). The field workers would use separate “collection bag” with unique identification number for collecting the discarded packs in each area. The pack collection from streets would take place simultaneously during the day when the “collection bag” to the retailers would be distributed. The street selection would also consider the street condition for walking and possibility of finding littered packs. Necessary safety equipment such as masks and gloves will be provided to the field staff while collecting littered packs. 

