Another important potential limitation of the proposed methodology would be its ability of correct estimation for the size of illicit market. Since the unit of observation from where packs would be collected is retail cigarette shops, selection bias might remain present in the estimation. The estimate would be overestimated if pack collection takes place in an area where illegal tobacco products are known to be traded. In contrast, the estimates would be underestimated if retailers purposefully preserve the licit cigarette packs in the collection bag. Moreover, conditioning that illicit cigarettes are sold in full packs in general rather than single sticks, collecting empty packs from retailers might underestimate the magnitude. Considering all these potential threats, we expect the study would be free from selection bias as the retailer selection would be completely random covering the urban–rural and border–non-border perspective around the country. The validity and representativeness of the estimate measured using the packs collected from retailers would be ensured by comparing that with the estimate retrieved from littered packs from the streets and packs collected from the trash recycle market in the same neighborhood. Estimates from the two later sources to a greater extent would address the limitations if retailer deposit only licit packs or illegal cigarette happens to be sold in full pack. The comparison of results and further analysis of illicit packs from these three sources would help us to examine the existence of any systematic difference among them. Absence of systematic difference would ensure the possible unbiasedness of the estimates [12].

Finally, in the absence of any prevalence data at the division or district level, it would not be possible to propose a sample size weighted on the local smoking prevalence or smoking intensity. Bangladesh has completed two rounds of Global Adult Tobacco Survey (GATS). However, the first round does not have district level or divisional level information on smoking prevalence while the data from second round have not been released yet. 

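### Agreement between retailer, street and trash packs from the same neighbourhood cannot show that the estimate is representative or free of area-selection bias, as section 4 claims

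*Protocol article*

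**What the plan says.** The limitations paragraph of section 4 (Discussion) names three threats to the retailer estimate. The first is area selection: "The estimate would be overestimated if pack collection takes place in an area where illegal tobacco products are known to be traded". The other two are that retailers may put only licit packs in the bag, and that illicit cigarettes may be sold by the full pack and so leave no empty pack with the retailer.

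The paragraph then makes four statements:

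1. It expects no selection bias, because retailers are said to be chosen wholly at random across urban, rural, border and non-border areas.
2. "The validity and representativeness of the estimate measured using the packs collected from retailers would be ensured by comparing that with the estimate retrieved". The comparators it goes on to name are street litter and recycle-market packs, both taken in the neighbourhood of the same retailers.
3. Of the street and trash estimates it says that, for the most part, they "would address the limitations if retailer deposit only licit packs or illegal cigarette happens to be sold in full pack".
4. "Absence of systematic difference would ensure the possible unbiasedness of the estimates".

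Section 2.2.2 places the street collection: "discarded packs from the streets where those retailers are established and also from some other locally important streets around public gathering places". Section 3 works on the assumption that litter by and large mirrors what shops on the same street sell.

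**The concern.** Statement 3 credits the comparison with the two retailer-side threats, which it can address. Statements 2 and 4 go further, to representativeness and to unbiasedness in general. Representativeness is a matter of which places were sampled, and comparing several kinds of pack from the same places carries almost no information on that.

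The proportion is meant to inform revenue authorities and to counter industry claims; the Introduction cites an industry-derived figure of about 2%. If the three sources agree, a reader who follows statements 2 and 4 would take an area-driven error as ruled out when nothing in the comparison tested for it.

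**Working it through.** **Step 1: what the comparison can see.** Let the true national share be θ, the area effect of the sampled places A, and the source-specific biases b_R (retailer), b_S (street) and b_T (trash). Then

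- p_R = θ + A + b_R, p_S = θ + A + b_S, p_T = θ + A + b_T
- p_R − p_S = b_R − b_S, and p_R − p_T = b_R − b_T

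A drops out of every difference. Withheld illicit packs and full-pack sale act through b_R and can produce a difference. Area selection acts through A and cannot, as far as the sources share it. That they largely do follows from the document: street packs come from the retailers' own and nearby streets, trash packs from the same neighbourhood, and section 3 assumes that litter resembles local sales.

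**Step 2: does random selection cover the area threat?** The inputs are section 2.1, section 2.2.1 and Tables 1 and 2.

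- Border districts: 4 + 6 + 4 + 4 + 6 + 7 = 31. Non-border districts in the same six divisions: 0 + 2 + 4 + 0 + 4 + 4 = 14. Non-border districts in all: 14 + 13 + 6 = 33. Total: 31 + 33 = 64. Table 1 adds up.
- In the six border divisions only border districts are eligible, so 14 of 64 districts have no chance of selection.
- Post codes: 6 × 10 = 60 in border districts and 2 × 10 = 20 elsewhere. The border share is 60/80 = 75% of post codes against 31/64 = 48.4% of districts.
- Table 2 also takes the five non-urban post codes of each border district from areas that share the land border: 6 × 5 = 30 of the 80.
- Within a post code the team determines a central point and approaches every eligible shop within half a kilometre each way. No random draw of retailers is described.

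Districts and post codes are drawn at random, but from a frame tilted towards the border. Retailers are not drawn at random.

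**Step 3: illustration of size.** The document gives no illicit share by border status. Assume p_N = 2% in non-border districts, equal weight per post code in the sample, and equal weight per district nationally.

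- Sample = (60 p_B + 20 p_N)/80
- National = (31 p_B + 33 p_N)/64

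| Border share p_B | Sample | National | Ratio |
|---|---|---|---|
| 2% | 160/80 = 2.0% | 128/64 = 2.0% | 1.00 |
| 4% | 280/80 = 3.5% | 190/64 = 2.97% | 1.18 |
| 6% | 400/80 = 5.0% | 252/64 = 3.94% | 1.27 |
| 10% | 640/80 = 8.0% | 376/64 = 5.88% | 1.36 |
| 20% | 1240/80 = 15.5% | 686/64 = 10.72% | 1.45 |

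In every row all three sources can have the same expected value, so they can agree fully whether the estimate is on target or 45% too high.

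**The case against.** Four points can be made for the protocol.

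**It answers area selection by sampling, not by the source comparison.** This is a fair reading of statement 1, and statement 3 limits street and trash packs to the two retailer-side threats. But the sampling answer does not fit the design (step 2), and statement 2 still attaches representativeness to the comparison.

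**The text is hedged, and it is Discussion prose.** It speaks of possible unbiasedness, and the Analysis Plan contains no pass/fail rule; it reports separate estimates and assesses how far they correspond. A reader might infer that the study will formally certify its headline figure. The document does not say so. The hedge, however, stands only in statement 4; the claim on representativeness has none.

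**Cancellation need not be exact.** Street packs also come from other local streets, and section 3 notes that litter may include legal duty-free and foreign packs. This stands, and it is why the point is limited to bias that is largely shared. A remaining difference of this kind would not measure area selection either.

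**No error rate can be attached to the comparison.** A reader might infer that the check passes about 95% of the time whatever the area bias. That figure is one minus an assumed 5% significance level. The document fixes no test, level or margin. In simulations with assumed pack counts and no mean difference between sources, the pass rate of an overall 5% test ran from about 0.43 to 0.975, depending on how packs vary between post codes and sources. Three pairwise tests went as low as 0.33, and a calibrated 1% test would pass 99%. No single pass rate belongs to this protocol.

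**Conclusion.** The point holds as a limit on inference. Agreement between the three sources can support the absence of retailer-specific bias. It cannot support representativeness or unbiasedness in general, because area selection is largely common to the sources. That part is logic and needs no assumed rates.

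The exposure is real because the frame leaves out 14 of 64 districts and puts 75% of post codes in border districts. Its size is unknown. The excess of 18% at a border share of 4%, or 36% at 10%, rests on the assumed 2% non-border share and on the equal weights in step 3. A reader might take these as estimates of the study's bias, but the document gives no rates from which to estimate it. If border shares were lower than non-border shares, the error would run the other way.

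**What to change.** In section 4, change the two sentences on what the comparison ensures. Agreement between retailer, street and trash estimates should be read as evidence against biases specific to the retailer source (withheld illicit packs, full-pack sale) and nothing more. Remove the claims that agreement ensures representativeness or general unbiasedness.

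State that area representativeness is not tested by this comparison, whatever its result. List the border-weighted frame as a limitation: border districts only in six divisions, 14 of 64 districts excluded, and 60 of 80 post codes in border districts. Bring the sentence on random retailer selection into line with section 2.2.1, under which all eligible shops around a team-chosen point are approached.

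This needs no new data and no change to sample or analysis. The cost is a less favourable claim about what agreement proves. It does not remove any area bias; it stops the comparison from being read as having excluded it.

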### 2.1. Study Sites and Sampling Design

Bangladesh is divided into eight administrative divisions (highest administrative unit) and 64 districts. Bangladesh also has large international land borders with neighboring countries, and therefore 31 districts in six divisions border with India and Myanmar (Table 1). In Appendix A, Figure A1 presents the map of Bangladesh where the green colored places represent the two divisions with no land border area and the rest share land borders with neighboring countries. 

We will use post codes as the primary sampling unit (PSU) and select PSUs using a multi-stage random sampling technique [14]. In a division having districts with borders, we will only consider those districts having borders for inclusion in the study, and randomly select one such district from the division. For instance, while considering Rajshahi division, among eight districts, four (namely, Naogaon, Rajshahi, Nwabganj, and Joypurhat) have areas with a land border. Therefore, the sampling frame would consist of those four districts only and one will be randomly selected. In two divisions, Dhaka and Barisal—where there is no district with international land border—we will randomly select one district from each. For example, in Barishal division, there are six districts (namely, Bhola, Barishal, Barguna, Pirojpur, Patuakhali, and Jhalokathi) and none of them have international border, hence all of them would be considered in the sampling frame for the purpose of random selection. Hence, eight districts will be selected, one from each division. 

Within a district, we will select 10 post codes randomly, 60 post codes from border and 20 from non-boarder districts—a total of 80 post codes from eight districts. The PSUs in each district will also be stratified by rural (five post codes) and urban (five post codes) to ensure maximum geographical variation. Post codes (PSUs) under city corporation or paurasava (municipality) will be defined as “urban” while postcodes outside of those places will be considered as rural. Currently, there are 1216 post codes, each with an average area of 121 square kilometers. The list of the post codes is available by districts and sub districts [18]. Table 2 illustrates the sampling design. 

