#### 2.2.3. Collecting Discarded Packs from Trash Recycle Markets

A common practice in Bangladesh is to recycle waste papers, including cigarette packs, which are then used as raw material in paper mills. Large municipal cities in urban areas locally known as “City Corporations” have a trash collection system. They collect trash from confined areas and from street corners where the trash bins are placed. A trash recycle market exists in some places to collect used papers and cigarette packs, but this is limited in rural areas. If a trash recycle market exists in the sample areas, and we are able to obtain the empty packs, we will include them in the study. 

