In general, all pack characteristics considered for detecting legitimacy in the retailer sample might also be accepted for those in littered or trash samples. Nevertheless, one of the limitations of the above general approach is that it might fail to distinguish between tax evasion and avoidance. More specifically, there may be some legally purchased duty-free packs as well as those bought from neighboring countries, in a sample from street, while also having illegally purchased and illegally sold packs in the retail shops belonging to that street. This possibility might result in under- or overestimation of the illicit cigarette trade. Hence, it rationalizes the application of an adjustment factor while measuring the magnitude of illicit cigarette in the sample collected particularly from street and trash recycle market. Table 3 exemplifies a thematic presentation of legitimacy criterion of a cigarette pack and adjustment requirement in the estimation. 

Assuming that the littered packs in the streets would by and large reflect the average characteristics of those sold by different retailers on the same street, the following adjustment method would be applied:

Suppose DF_L_ is the proportion of duty-free packs (both legal and illegal) in the littered sample and DF_R_ is the proportion of duty-free packs (all illegal) in retailer sample. Then, the estimated proportion of illegal duty-free packs from littered sample would be
=DF_R_ if DF_L_ > DF_R_; and
=DF_L_ if DF_L_ ≤ DF_R_.   

Similar adjustment process would be followed while estimating extent of illicit cigarette using packs from trash recycle sample. It should be noted here that self-made cigarette using tax-paid tobacco powder or crushed tobacco may not be the scope of current work. However, a pack for a local category of cheap cigarette known as “birri” would be collected and examined for its compliance as per the study definition. Statistical Analysis (STATA) software version 15 would be used. The main statistical analysis will report the frequencies and proportions of cigarette packs that do not comply with the tobacco control laws and falls within the study definition of illicit. 

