The packs collected from different sources would be kept in separate bags and analyzed separately. In addition, the features of the respective packs would be recorded in three different databases to find separate estimates of illicit cigarettes. The estimates from first two inter-related methods will be triangulated and hence complementing each other. We will then compare and validate these findings with the third method. Given the availability of the trash market in the study sites, and adequate volume of packs collected from the trash market, the findings will be compared with the first two methods. We will assess the extent to which the result of trash market measure corresponds to first two measures to estimate of illicit trade for its validity. Findings from pack analysis would be further triangulated with the retailer interview findings for better understanding of the pattern of illicit practices in the cigarette market. 

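### Finding no systematic difference between pack sources is taken to secure the validity and unbiasedness of the estimates, which does not follow

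*Protocol article*

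**What the plan says.** Section 4 (Discussion) lists threats to the retailer estimate, including retailers keeping only licit packs for the collection bag and illicit cigarettes being sold as whole packs. It answers them by comparison across sources: "The validity and representativeness of the estimate measured using the packs collected from retailers would be ensured by comparing that with the estimate" from street and trash packs. It concludes: "Absence of systematic difference would ensure the possible unbiasedness of the estimates".

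Section 3 (Analysis Plan) is milder. On the new trash-market method it says: "We will assess the extent to which the result of trash market measure corresponds to first two measures". The main analysis is descriptive: "The main statistical analysis will report the frequencies and proportions of cigarette packs". The trash comparison depends on there being an "adequate volume of packs collected from the trash market", with no number attached.

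Two other statements bear on what agreement can mean. Section 3 sets the illegal duty-free share of littered packs to the smaller of the littered and retailer shares, and treats trash packs similarly. Section 4 excludes every pack whose tax stamp is not in a state to be checked.

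**The concern.** Validating one source against another is a question of agreement. The Discussion answers it from the wrong side: it takes the absence of an observed difference as the assurance. The fewer the packs or post codes, the more easily that condition is met, so weak data are rewarded.

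The comparison carries much weight. It is the stated answer to under-reporting by retailers, the basis of research question (c) on the trash-market method, and part of the support for using the findings to counter industry claims. If the inference stands, the study could call a retailer estimate valid when the comparison had little capacity to show otherwise.

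**Working it through.** **The plan's own design figure.** Section 2.1 gives "a total of 80 post codes from eight districts": 8 × 10 = 80, of which 6 × 10 = 60 are in border districts and 2 × 10 = 20 in non-border districts. This reproduces, but it says nothing about the precision of a comparison between sources.

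**Inputs.** From the Introduction: an industry-based illicit share of about 2% for Bangladesh and 16.8% for low- and middle-income countries. Assumed, because the article does not state them:
- m = 25 to 100 packs per source per post code
- intraclass correlation (ICC) of 0.05 to 0.10 between post codes
- a two-sided 5% test
- a retailer share that is half the comparator share

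**Closed-form check, sources independent.** Design effect = 1 + (m − 1) × ICC. Effective n = post codes × m / design effect. SE = √{[p₁(1 − p₁) + p₂(1 − p₂)] / effective n}. Chance of no significant difference ≈ Φ(1.96 − (p₂ − p₁)/SE).

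- 80 post codes, m = 25, ICC 0.10: design effect 1 + 24 × 0.10 = 3.4, effective n = 2,000/3.4 = 588.
  - 2% v 4%: SE = √(0.0580/588) = 0.0099, z = 2.01, missed 48%.
  - 5% v 10%: SE = √(0.1375/588) = 0.0153, z = 3.27, missed about 9–10%.
  - 8.4% v 16.8%: SE = √(0.2167/588) = 0.0192, z = 4.38, missed under 1%.
- 80 post codes, m = 100, ICC 0.05: design effect 5.95, effective n = 8,000/5.95 = 1,345. At 2% v 4%: SE 0.0066, z = 3.05, missed 14%.
- 20 post codes at 2% v 4%: m = 25, ICC 0.10 gives effective n 147, z = 1.01, missed 83%; m = 100, ICC 0.05 gives effective n 336, z = 1.52, missed 67%.

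**Simulation check.** Beta-binomial packs within post codes and a paired t-test on post-code differences, over the same ranges of m and ICC.

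| Retailer v comparator | Post codes | Between-source correlation | No difference found |
|---|---|---|---|
| 2% v 4% | 80 | 0 | 13–49% |
| 2% v 4% | 80 | 0.5–0.8 | about 0–32% |
| 5% v 10% | 80 | 0 | 0–9% |
| 8.4% v 16.8% | 80 | 0 | 1% or less |
| 2% v 4% | 20 | 0 | 68–85% |
| 8.4% v 16.8% | 20 | 0 | 12–43% |

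The 20-post-code rows illustrate trash packs. Section 2.2.3 says "A trash recycle market exists in some places to collect used papers and cigarette packs, but this is limited in rural areas", and half the sampled post codes are rural. The actual number with a usable market is unknown.

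**Agreement by construction.** The adjusted littered duty-free share is min(DF_L, DF_R). If DF_R = 2% and DF_L = 4%, the adjusted value is 2% and the difference is 0 at any sample size. On this component the adjusted street share can never exceed the retailer share, which is the direction in which retailer under-reporting would show.

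**Shared bias.** Packs whose stamp cannot be checked are dropped from all three sources. If they are more often illicit, every source is too low together, and agreement reveals nothing.

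**The case against.** The article names no test, significance level or pass/fail threshold. Section 3 speaks of the extent of correspondence, which is graded estimation, and a 2% versus 4% result reported as such need not be read as no difference. The criticised sentence says only that unbiasedness is possible. A margin and an interval method could sit in a full protocol or analysis plan that is not shown. The study counts a pack as illicit if it fails any one of seven attributes, so the measured share may be well above the 2% industry figure, where a two-fold gap is rarely missed with 80 post codes. Street and retailer packs also come largely from the same streets, so the comparison gains from pairing.

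Most of this stands. A reader might infer that the plan contains a significance-test rule which would pass a retailer estimate wrong by a factor of two. The documents do not support that: no such rule is written, and the miss rate runs from negligible to about one half with 80 post codes, depending on unstated quantities. Nor is the absence of a margin from the article a fault in itself.

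What does not fall away is the stated inference. The word for possible is outweighed by two statements in the same section that the comparison ensures the result. Nothing in Section 3 corrects it, and an analysis plan that supplied a margin would not undo the published claim. The duty-free cap and the shared stamp exclusion are independent of sample size and of any choice of test.

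**Conclusion.** The concern holds as a fault in the stated inference. Agreement between sources supports the retailer estimate but cannot ensure its validity or lack of bias, because the comparison may be imprecise, because the sources may share a bias, and because part of the agreement is built in by the duty-free cap.

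The size of the imprecision problem is conditional. It matters if the illicit share is near 2% or if few post codes yield packs from both sources. It is small at 5% versus 10% with all 80 post codes and negligible at 8.4% versus 16.8%. These figures rest on the assumed pack counts, clustering and test. The descriptive proportions from each source are unaffected; what is affected is the claim of validation.

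**What to change.** In Section 4, replace the two statements that the comparison ensures validity and unbiasedness with wording that agreement supports but does not establish unbiasedness, and say that it cannot exclude a bias shared by all sources.

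For each pair of sources, report the difference in illicit proportion before as well as after the duty-free adjustment. Use the post codes where both sources yielded packs, and give a confidence interval that respects post-code clustering and pairing. Claim that the retailer or trash estimate is validated only if that interval excludes differences the investigators fixed beforehand as important; otherwise report that agreement was not shown. Apply the same rule to the validity assessment in Section 3.

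The margin should be on a scale suited to the expected illicit share. A fixed 1 percentage point would not serve. With both sources truly at 2%, 4,000 packs each and a design effect of 5 to 10 (effective n 800 to 400), the 90% half-width is 1.645 × √(2 × 0.02 × 0.98 / effective n) = 1.2 to 1.6 points, already wider than the margin.

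The cost is a few sentences and one interval per comparison before and after adjustment, with no new data. The downside is that the report may often be unable to claim validation.

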This protocol will present a mixed-methods study to estimate the extent of illicit cigarette trade in Bangladesh. Three research questions will be addressed: (a) What proportion of cigarettes sold as retail in Bangladesh are illicit? (b) What are the common types of tax avoidance and tax evasion in Bangladesh? (c) Can pack examination from trash recycle market be considered as a new method to assess illicit trade in comparison to that from retailers and streets? Findings from this study will help policy makers develop more effective tobacco control measures and refute industry claims in Bangladesh. 

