### 2.2. Data Collection and Management

From each PSU, three methods will be used—collecting packs from: tobacco retailers; those discarded in the street; and those discarded in trash recycle markets. An interview of the same cigarette retailers supplying packs for the study will also be carried out. 

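### The trash-market comparison is not clearly confined to post codes that have a trash market, and agreement between sources is credited with more than it can show

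*Protocol article*

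**What the plan says.** The Introduction poses the third research question: "Can pack examination from trash recycle market be considered as a new method to assess illicit trade in comparison to that from retailers and streets".

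On coverage, Section 2.2 states "From each PSU, three methods will be used". Section 2.2.3 says "A trash recycle market exists in some places to collect used papers and cigarette packs, but this is limited in rural areas", and takes trash packs only where a market is found and the packs can be obtained. Section 2.1 plans "60 post codes from border and 20 from non-boarder districts—a total of 80 post codes from eight districts", with five urban and five rural post codes in every district. Table 2 places the rural post codes of the six border districts in sub-districts that lie on the border.

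On analysis, Section 3 builds a separate database and a separate estimate for each source. It compares the trash estimate with the other two if markets are available and enough packs are found: "We will assess the extent to which the result of trash market measure corresponds to first two measures". The same section sets the illegal duty-free share of the street sample to the retailer proportion whenever the street proportion is higher, and applies a similar rule to trash packs.

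The Discussion relies on street and trash packs to offset the risk that retailers hand in only licit packs. It ends that argument with "Absence of systematic difference would ensure the possible unbiasedness of the estimates".

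**The concern.** There are two linked problems.

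The first is who is compared with whom. If the trash packs come mainly from urban post codes while the retailer and street estimates draw on all post codes, a difference may reflect where the packs came from and not how they were collected. It can also work the other way, with a faulty trash method matching the pooled figure by accident. Section 3 does not settle this, and Sections 2.2 and 2.2.3 disagree on whether trash packs come from every post code.

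The second is what agreement proves. Sources that agree may share an error. One component is also made to agree in part by the analysis rule itself, because the street and trash duty-free shares may not exceed the retailer share. That weakens the comparison exactly where the Discussion wants it to work, namely in exposing retailers who withhold illicit packs.

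At stake is the answer to question (c), one of the three questions of the study, and the reassurance that the retailer estimate is meant to draw from the other two sources.

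**Working it through.** **1. The design figures reproduce.** Section 2.1: 8 districts × 10 = 80 post codes; 6 × 10 = 60 in border districts and 2 × 10 = 20 elsewhere. Urban: 8 × 5 = 40. Rural: 8 × 5 = 40. From Table 2, 6 × 5 = 30 of the 40 rural post codes are in border sub-districts. The places least likely to have a trash market are therefore largely those chosen to capture border trade.

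**2. Size of a geography effect.** The article gives no illicit share by urban or rural area, so the shares here are assumed. Suppose every post code counts equally, trash packs come only from urban post codes, and every method is free of error. Then the pooled share is (40 × urban + 40 × rural) / 80, and the trash share equals the urban share.

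| Urban | Rural | Pooled retailer or street | Trash | Gap (points) |
|---|---|---|---|---|
| 2% | 2% | 2% | 2% | 0 |
| 2% | 5% | 3.5% | 2% | 1.5 |
| 5% | 10% | 7.5% | 5% | 2.5 |
| 2% | 10% | 6% | 2% | 4 |
| 10% | 20% | 15% | 10% | 5 |

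The gap is half the rural-urban difference and vanishes when the two shares are equal. The reverse also holds. In the 2% and 10% row, a trash method that read 6% in urban areas, 4 points too high, would appear to agree perfectly with the pooled 6%.

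**3. The adjustment rule.** Section 3 gives the adjusted duty-free share as min(DF_L, DF_R), where DF_L is the littered-pack proportion and DF_R the retailer proportion. Two consequences follow.

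- The adjusted street or trash value can never exceed DF_R. On this component those sources can only agree with the retailers or fall below them.
- If retailers withhold all duty-free packs, DF_R = 0 and the adjusted value is min(DF_L, 0) = 0, whatever was found in the street or the trash. The three sources then agree at zero because of the rule.

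**4. The Discussion sentence.** If every source is shifted by the same amount, all differences between sources are zero and all estimates are wrong. One candidate lies in the article: packs whose tax stamp cannot be checked are excluded from all sources. If stamp damage is related to illicit status, that exclusion can shift all three estimates. Whether it does is unknown, and a comparison of the sources would not show it.

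**5. Precision of a matched comparison.** If only urban post codes had a market, at most 40 of the 80 could contribute. No pack numbers are given. Assume a 5% share, n packs per source, design effect D and independent sources. The half-width of the 95% interval is 1.96 × √(2 × 0.05 × 0.95 × D / n).

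- n = 500: 2.7 points at D = 1, and 4.7 points at D = 3.
- n = 2000: 1.4 points at D = 1, and 2.3 points at D = 3.

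**The case against.** The strongest reply is that the article does not commit to an unmatched comparison. A reader might infer that the trash estimate will be set against packs from all 80 post codes, but no sentence says so. The Discussion speaks of trash packs from the retailers' own neighbourhood, and Section 3 makes the comparison depend on markets being available and volume being sufficient. If the matching is local, the gaps in the table do not arise. This stands as a limit on the point: the fault is that the restriction is not clear, not that the wrong comparison has been fixed. The neighbourhood remark occurs in the Discussion, about the retailer estimate, and Section 3 does not carry it over.

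A reader might also infer that the method will be declared valid on a non-significant test. The article names no test. Section 3 speaks of the degree of correspondence, and the Discussion sentence is hedged by the word possible and mainly concerns the retailer estimate. That too is accepted. The objection here is to the inference from agreement to absence of bias, which needs no significance test to be unsound.

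Nor do the documents support the view that question (c) cannot be answered at all. A comparison within market areas would inform it for those areas, and Section 2 offers the method for settings where such markets are established.

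The defence can fairly add that some biases are not shared. Selective deposit by retailers and full-pack sales affect retailer packs, and street and trash packs help to reveal them. The stated cap concerns duty-free packs only. Detailed statistics may also sit in a fuller plan. But the sentence on unbiasedness, the cap and the conflict over coverage are all in the published text.

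**Conclusion.** The point holds in this limited form and should be acted on. Section 3 does not clearly confine the comparators to post codes with a trash market, while Sections 2.2 and 2.2.3 give different accounts of where trash packs come from. If the comparison were unmatched, geography alone could produce a gap of 0 to 5 points. That range rests on the assumed shares, an urban-only trash sample and equal weight per post code, and it is zero if urban and rural shares do not differ.

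The other two parts do not depend on those assumptions. Agreement between sources cannot exclude a bias common to them, and the cap at the retailer proportion builds in part of the agreement on duty-free packs. How much this matters depends on how common duty-free packs are, which the article does not say.

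**What to change.** For question (c):

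- Compare sources only within post codes where retailer, street and trash packs were all obtained.
- Use the shares before the duty-free cap. Show the duty-free component separately, since uncapped street and trash shares may include legally bought duty-free packs.
- Report the paired differences between sources with 95% intervals that respect clustering by post code.
- Limit the conclusion to areas with trash markets.

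In the Discussion, replace the quoted sentence with wording such as: *Agreement between the sources would support their consistency but would not exclude biases shared by all of them.* Reconcile Section 2.2 with Section 2.2.3, so that trash packs are described as collected only in post codes where a market exists and packs can be obtained.

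The cost is wording and a different analysis of data that will be collected anyway. The drawback is that fewer post codes enter the comparison, so its intervals may be wide and the result inconclusive, which should then be reported as such. No particular equivalence margin is asked for here.
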